## Abstract

**Background:**

Child health and development can be promoted by strengthening and supporting parents. Research on parental support programs based on positive psychology and a health-promoting approach aimed at all parents, and in particular parents of infants is limited. All Children in Focus (ACF) is a parental support program that has been evaluated in a randomized trial in parents of children 3–12 years. The ACF is based on health promotion aiming to increase parents’ confidence and child’s well-being. In the current study, we will study the effects of a revised version of the ACF called *Little ACF* adapted to parents with children aged 1–2 years.

**Methods:**

The study includes a randomized controlled trial (RCT) taking place at several Child Health Centers (CHCs) in Sweden. The RCT will evaluate the efficacy of *Little ACF* (intervention) in comparison with four digital lectures about child development and parenting (active control). Parents are recruited at the 10-, 12-, or 18-month visits to CHC by CHC-nurses. Data to assess changes in parental competencies and child socio-emotional development are collected through online questionnaires completed by parents at five time points: baseline, post-intervention, after 6 and 12 months, and when the child is 3 years old.

**Discussion:**

The paper describes a study protocol of a randomized controlled trial evaluating the effects of a parental support program during infancy. Several issues related to the methodology and implementation are discussed.

**Trial registration:**

ClinicalTrials.gov NCT05445141. Registered on 6 July 2022.

## Introduction

### Background and rationale {6a}

It is of utmost importance and interest for society to promote children’s development and well-being by creating good opportunities for parents. One way to strengthen parents is through programs that promote children’s health or prevent ill health [1]. Most prevention programs offered to parents are primarily aimed at parents with acting-out children [2]. Universal programs delivered to all parents based on positive psychology [3] and health promotion [4] have not been studied to the same extent [5, 6]. Positive psychology was introduced by Seligman in the 1990s and focuses on various components that relate to well-being; i.e., positive emotions, engagement, relationships, meaning, and achieving one’s goals [7, 8]. Within positive psychology, the concept of “self-efficacy” — belief in one’s own ability — has also been described as an important part of well-being [9].

Health promotion is described by the World Health Organization (WHO) as a process where the individual can take control and improve their health through participation and commitment [10]. Well-being is also an important concept within health promotion although ill-defined. According to positive developmental psychology, well-being during infancy is promoted through the development of emotional regulation [11]. Emotional regulation is developed in interaction with parents through mirroring, putting words to the child’s feelings, and by showing positive feelings for the child. Parents need to support each other and be role models for the child [12, 13]. This is also in line with what is presented in the theory of coparenting, which describes how parents need to develop mutual trust and agree on the distribution of responsibilities, values about child rearing, and how conflicts can be handled [14]. A positive parental relationship is an important component for the child’s well-being according to positive developmental psychology [12].

In a meta-analysis of studies that evaluated support (mostly prevention) to parents with children between 0 and 7 years of age, it emerged that parental support including communication of feelings showed effects on parents’ behavior. Opportunities to practice skills showed greater effects on parents’ behavior and child externalizing problems [2]. The largest effects for parents were increased parental efficacy and for children a reduction in internalizing problems [2].

The state of evidence for universal parenting programs [1] is still limited and programs aimed at parents with infants are unusual, despite the fact that parenthood in this period may contain many challenges [15]. In summary, there is a great need to develop and evaluate promotional efforts aimed at parents with infants.

All Children in Focus (ACF) is a parental support program based in health promotion that was developed and evaluated in Sweden for parents of children aged 3–12 years [16]. ACF is developed based on research and was developed in dialog with parents and professionals. A randomized controlled trial (RCT) found that ACF 3–12 years increased parents’ confidence and well-being of the child [16]. Here, we are testing a revised version of ACF called *Little ACF* in Swedish that is adapted to parents with children aged 1–2 years.

### Objectives {7}

The aim of the study is to increase the knowledge on the effects of *Little ACF* on parents and children.

Our specific research questions are how *Little ACF* can:Strengthen strategies of emotional regulation in parents,Promote parenting practices,Promote child socio-emotional well-being,Lead to the reduction of child behavior problems (externalizing/internalizing), andEngage and retain parents in groups?

### Trial design {8}

The study includes a two-arm parallel superiority RCT to evaluate the efficacy of *Little ACF* in comparison with four digital lectures covering child development and parenthood. The allocation ratio applied was 1:1.

## Methods: participants, interventions, and outcomes

### Study setting {9}

The study is conducted in collaboration with thirteen Child Health Centers (CHCs) in Sweden. The included CHCs had registered interest to the request that was sent out to all CHCs in the Stockholm region for participation in the study Little ACF. To be included, the management at each CHC also had to appraise that the CHC had sufficient capacity in terms of employed nurses to ensure participation. The included CHCs are situated in the region of Stockholm, and a few of them are located in commuting municipalities of Stockholm and others in small towns, altogether representing both urban and rural areas. Additional CHCs might be included in the study before recruitment is finished. The specific names of the included CHCs are not presented to reduce the risk of bias in the assessment of the study.

Today, all families in Sweden are offered ten individual appointments at the local CHC before the child turns 18 months [17]. Parents are often invited to participate in some form of parenting groups when the child is between 2 and 11 months, but the content of these groups varies greatly, and the efficacy of those groups has never been evaluated scientifically. The content is usually focused more on the child’s development than on parenting [18] and the groups mainly reach mothers [19].

Given that almost all families with young children attend the Swedish CHCs, it is a highly relevant arena for the development and evaluation of additional structured parenting support efforts [17] and a natural place for both recruitment and implementation.

### Eligibility criteria {10}

#### Inclusion criteria

Parents of children in the age group 1–2 years who are registered at any of the included CHCs

#### Exclusion criteria

Parents in need of interpreters

### Who will take informed consent? {26a}

For the group leaders, a preliminary consent via phone or email was provided in relation to registering to the training. Written consent was then collected at the first training occasion.

At the child’s ordinary 10-, 12-, or 18-month visit at the CHC, the CHC-nurse informs the parents about the study orally and provides them with an information flyer about the study. Parents who declare interest in participation receive an email with a link to a study-specific website. On the website, they sign the consent digitally if they wish to participate and then complete a digital baseline questionnaire. All caregivers to the child are encouraged to participate.

## Interventions

### Explanation for the choice of comparators {6b}

Parents who are assigned to the control group are offered four recorded digital lectures that are available for about four weeks. The lectures are 10 to 19 min long and include age-appropriate information about parenthood and child development. The lectures are information-based without providing parenting strategies. The themes are (1) food and eating, (2) sleep, (3) child accidents and infections, and (4) curiosity as a driving force in child development. A waitlist control design was considered as an alternative to the four recorded digital lectures, but this was not regarded as possible due to the long follow-up time of the participants and the narrow timespan of when the intervention is meant to take place (when the children are 12–24 months). The decision to offer lectures to the control group was made based on suggestions from the group leaders from the pilot study to increase the chances of recruiting and retaining participants in the control group by offering some kind of additional activity on top of usual care since no reimbursement is provided to the participants and since wait-list control group was not possible.

### Intervention description {11a}

#### The intervention *Little ACF*

The program *Little ACF* is based on the parental support program ACF for parents to 3–12-year-olds [20]. *Little ACF* was developed focusing on children 1 to 2 years, a period in life when families go through many changes [15]. During this year, the child usually starts preschool, parents go back to work or studies, and the support from CHC gradually declines with the visits becoming less and less frequent. During this period, fathers are often on parental leave and may therefore be more likely to participate in parental groups.

The adjustment of the program ACF to *Little ACF* has been realized through a collaboration between CHCs in Region Stockholm, the unit PLUS in Stockholm municipality, and the Center for Epidemiology and Community Medicine (CES) in Region Stockholm. The final version of *Little ACF* was developed and finalized by CES. The content of *Little ACF* is based on research on parenthood and child development, the United Nations Convention on the Rights of the Child, and expressed needs and wishes of parents of small children. The material was tested in a pilot study in 2021 when 10 group leaders were trained and led five parent support groups. The pilot led to a revision of the material including a stronger focus on emotional regulation and secure relationships. Figure 1 shows a logic model of how *Little ACF* is assumed to lead to outcomes in parents and children.

**Fig. 1 Fig1:**
[figure not shown]
Logic model for how *Little ACF* can lead to outcomes in parents and children

The program *Little AFC* consists of four group meetings with four different themes (described in Table 1). The theoretical foundation is positive psychology including research about attachment, parenting and coparenting, emotional regulation, and observational learning [15]. Each group is led by two group leaders of which one is a CHC-nurse, and the other is a group leader from the municipal or civic society that works with parents of small children. The group meetings are scheduled to 60 min and the parents can thereafter stay and discuss and socialize for 30 min. The parents are allowed to bring their children to the group meetings due to the young age of the children.

**Table 1 Tab1:** Summary of the content of the group meetings in *Little ACF*

**Meeting 1** **Children are different**	The content of the first meeting deals with children’s innate temperament, how it can affect parenting, and how parents can strengthen self-esteem and security in their children. The meeting starts with a welcome session where participants present themselves and are provided with some practical information. The group leaders introduce *Little ACF*, explain the goal with the meetings and present the content of the current meeting. The themes for the first meeting are (1) temperament, (2) sensitive parenting, and (3) putting words to the child’s feelings. Theoretical elements are alternated with specifically designed illustrations, role plays, and group discussions. The meeting ends with an introduction to the example to try out at home that focuses on putting words to the child’s feelings. The printed material is distributed to the parents
**Meeting 2** **Being together**	The content of the second meeting focuses on infant development and how parents can regulate infant’s emotional expressions. The second meeting starts with the group leaders introducing the content of the meeting and a discussion about examples tested at the home. The themes of the second meeting are (1) autonomy, curiosity, and emotional expression; (2) challenging situations, (3) make everyday work; and (4) validate, explain, repeat, and distract. Theoretical elements are alternated with illustrations and group discussions. The meeting ends with an introduction to the example to try out at home that focuses on validation, explain, repeat, and distraction. The printed material is then distributed
**Meeting 3** **Regulation of parental emotions**	The content of the third meeting focuses on challenging parental feelings and how parents can regulate their own emotions and maintain sensitive parenting. The third meeting starts with an introduction to the topics and a follow-up on examples tested at home. The themes of the third meeting are (1) emotions are contagious, (2) stress, (3) the emotional curve, and (4) stop-think-act. Theoretical elements are alternated with illustrations and group discussion. The meeting ends with the introduction to the final home exercise focusing on testing the strategy Stop-think-act. The printed material is thereafter distributed
**Meeting 4** **Secure relations**	The last meeting focuses on the importance of secure relations for both parents and children, about separations, and how parents can help the child feel safe with other significant adults. The fourth meeting starts with the day’s topics and a follow-up on what has been tested at home. The themes of the fourth meeting are thereafter (1) a network of secure relations, (2) being away from each other, (3) catching the golden moments, and (4) closure. Theoretical elements are alternated with illustrations and group discussions. The meeting ends with group leaders informing about other available support to parents in their local community. Parents are provided the printed material including a list of available parental support

The content is based on role plays and discussion topics. The manual for the group leaders is structured similarly for all four meetings with clear instructions on what is expected by the group leaders at each stage for example when questions should be posed. The three first meetings end with an example to try at home and the following meeting starts with discussing these examples. The examples are designed to stimulate reflection among the parents and to encourage them to test new positive approaches in the interaction with their child. Parents will be distributed a printed material at each meeting that will also be available on a web-portal. The parents can use the web-portal between the meetings to read and share the content to the other parent or other significant adults around the child.

### Criteria for discontinuing or modifying allocated interventions {11b}

Participants are allowed to leave the study at any time without having to disclose the reason for doing so. If a participant decides to leave the study, data that have been collected until that point will be included in the analysis.

### Strategies to improve adherence to interventions {11c}

No reminders are sent out for the group meetings, or the lectures and no reimbursements are provided to the participants in the study. Group leaders fill out a questionnaire after each session about parental engagement and the group leaders adherence to the manual. Supervision to the group leaders is offered regularly during the trial to discuss enabling and aggravating circumstances during the sessions.

### Relevant concomitant care permitted or prohibited during the trial {11d}

Participants in both groups are attending care as usual with the ordinary visits to CHC. There are no restrictions on care or attendance to other parental interventions during the trial.

### Provisions for post-trial care {30}

No post-trial care is provided.

### Outcomes {12}

Data are collected at five time points (Table 2): baseline (T1 – infant age 12–18 months), post-intervention (T2 – infant age about 14–20 months), after 6 months (T3 infant age 18–24 months), after 12 months (T4 – infant age 24–30 months), and in conjunction with the CHC visit when the child is 3 years old (T5). The data are collected through questionnaires to the parents. The baseline questionnaire contains background questions on the age and sex of the child and the parent and questions on parental educational level, country of birth, and family composition as well as several validated instruments that are repeated in the follow-up questionnaires.

**Table 2 Tab2:** Time points for the specific outcome measures and intervention assessments

	**Time points**					
**Assessments**	**T1**	**Intervention**	**T2**	**T3**	**T4**	**T5**
***Parents***						
Baseline variables	X					
**Parental strategies:**						
Parental self-efficacy	X		X	X	X	X
Parent emotional regulation	X		X	X	X	X
Coping with child negative emotions	X		X	X	X	X
Parenting stress	X		X	X	X	X
Coparenting relationship	X		X	X	X	X
***Child well-being (through assessments of parents)***						
Child’s social and emotional development	X		X	X	X	X
Psychological and behavioral problems						X
***Group leaders***						
Checklists group leaders		X X X X				

#### Primary outcome

The primary outcome is five aspects of parenting strategies, measured at all five time points of the study (T1, T2, T3, T4, and T5). Parenting self-efficacy (PSE) [16, 20] is measured with 48 items that are assessed with an 11-point Likert scale from 0 (completely disagree) to 10 (fully agree) using a modified version of *Tool to Measure Parenting Self-Efficacy* (TOPSE) [21].

The emotional regulation of the parent in relation to the child is measured using the *Parent Emotion Regulation Scale* (PERS) developed by Pereira et al. [22]. The PERS consists of 20 questions that are to be answered on a scale from 1 (never or almost never) to 5 (always or almost always). For the purpose of our study, questions nr 1, 11, and 18 were removed based on a validation study of the PERS that took place prior to the study (Manuscript in preparation).

How parents handle children’s negative emotions is assessed using the *Coping with Toddlers’ Negative Emotion Scale* (CTNES) [23]. In its original version, 12 situations are described to which the parents should assess the likelihood of using 6–7 different strategies to solve each situation. The likelihood assessment ranges from 1 (not likely at all) to 7 (very likely). For this study, 8 situations (items 3–10) were selected based on the analysis from the validation of the Swedish version (Manuscript in preparation).

Parental stress is assessed using the scales *incompetency* and *role limitation* from the *Swedish Parenting Stress Questionnaire* (SPSQ) [24]. The items are assessed with 5 response alternatives.

Five questions inspired by the *Coparenting Relationship Scale* [25] are used to assess the quality of parents’ coparenting relationship. The answers range from 1 (not true at all) to 5 (very true) on a 5-point scale.

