### Sample size {14}

#### Power calculation

A previous RCT of the program ACF for parents of children 3–12 years of age showed an effect size (Cohen’s *d*) of 0.30 for parental self-efficacy [16]. We expect a slightly smaller effect (*d* = 0.25) because this study compares *Little ACF* with lectures while the previous study had a waitlist control group. A total of 251 participants in each group are therefore needed with a significance level of 95% (*p*-value 0.05) and a power of 80%. A drop-out of 25% is expected resulting in the need to include 670 families in total. Each group consists of parents to 5–8 children so about 60–70 groups are needed. Each group leader is expected to lead at least three groups which means that about 25 group leader pairs are needed in total.

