## Statistical methods

### Statistical methods for primary and secondary outcomes {20a}

The SPSS and R software will be used for all statistical analyses. Data will be tested for assumptions of parametric statistics. Examinations of pattern and amount of missing data will be performed and if appropriate treated by using relevant estimates. Statistical tests will be two-sided, and the level of significance will be set to 0.05.

Family and infant characteristics will at baseline be summarized overall and by trial arms, with means and standard deviations or medians and ranges for continuous variables. Numbers and percentages will be used for categorical variables. Summarized baseline measures regarding parental strategies and child well-being will also be shown. Any differences between groups at baseline will be examined with *t*-test for independent samples, chi-square test, or Mann–Whitney *U* test.

Fidelity measured as the group leader’s adherence to the program and parents’ participation in *Little ACF* or digital sessions will be summarized with descriptive statistics. Researchers performing statistical analyses of the primary outcome will be blinded to intervention allocation (*Little ACF* or digital session). Measures of effect size will be estimated to assess intervention effects. Hierarchical regression model will be used for assessing primary and secondary outcomes. Linear mixed regression model will be used for continuous data and generalized mixed models for binary and ordinal data. Intervention effects will be assessed for the primary outcome at the post-intervention and at the follow-ups with control for baseline scores. For the secondary outcome, intervention effects will be measured at the follow-ups with control for baseline and post-intervention scores.

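### Five instruments at several follow-ups share primary status at a general 0.05 level with no success rule, while the sample size covers one unadjusted comparison of parental self-efficacy

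*Protocol article*

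**What the plan says.** The Primary outcome section gives primary status to five measures at once: "The primary outcome is five aspects of parenting strategies, measured at all five time points of the study (T1, T2, T3, T4, and T5"). Each has its own instrument: parenting self-efficacy (modified TOPSE), parent emotion regulation (PERS), coping with toddlers' negative emotions (CTNES), parenting stress (two SPSQ scales) and five coparenting questions.

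The section Statistical methods for primary and secondary outcomes {20a} sets one general level: "Statistical tests will be two-sided, and the level of significance will be set to 0.05". On timing it says: "Intervention effects will be assessed for the primary outcome at the post-intervention and at the follow-ups with control for baseline scores". T1 is therefore the baseline adjustment, and T2, T3, T4 and T5 are the times at which effects are assessed.

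The Power calculation section starts from the earlier trial's effect size "of 0.30 for parental self-efficacy [16"] and lowers it: "We expect a slightly smaller effect (*d* = 0.25"). It concludes: "A total of 251 participants in each group are therefore needed with a significance level of 95% (*p*-value 0.05) and a power of 80"%. Then: "A drop-out of 25% is expected resulting in the need to include 670 families in total". No time point is attached to this calculation.

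**The concern.** The outcomes section and the sample-size section describe different primary analyses: five measures followed over time in the first, a single measure compared once in the second. Nothing in the article links them. It does not say whether success means one significant instrument, all five, or self-efficacy alone, or at which time.

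Which problem follows depends on that missing rule. If any one significant result is enough, the type I error of the primary claim exceeds 5%. If all five must succeed, the power of the primary claim falls below 80%. If self-efficacy leads, the design is sound, but the article does not say so. Its Objectives {7} point elsewhere: they list parental emotion regulation first and do not name self-efficacy. Without a declared rule, readers of the final report cannot tell a confirmatory result from one of several.

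**Working it through.** **Inputs from the protocol.** Five instruments (Primary outcome). Four post-baseline times (Outcomes {12} and section {20a}). Two-sided 0.05 ({20a}). d = 0.25, 251 per arm, 80% power, 25% drop-out, 670 in total (Power calculation). Allocation 1:1 (Trial design {8}). The protocol gives no correlations between instruments or over time, so those below are assumptions.

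**1. The stated sample size.** n per arm = 2(z₀.₉₇₅ + z₀.₈₀)²/d² = 2(1.960 + 0.842)²/0.0625 = 251.2. This matches the stated 251 (252 if rounded up). Drop-out: 502/0.75 = 669.3, so 670. Power at 251 per arm: d√(n/2) = 0.25 × √125.5 = 2.80, and Φ(2.80 − 1.96) = 0.80 (0.798 with the t distribution). The calculation is therefore one comparison of one outcome at an unadjusted 0.05.

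**2. Chance of at least one significant primary result when nothing differs.** For k independent tests this is 1 − 0.95ᵏ.

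- k = 5 (one test per instrument): 1 − 0.95⁵ = 0.226.
- k = 20 (five instruments × four times): 1 − 0.95²⁰ = 0.642.

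For results favouring the programme only, 0.975 replaces 0.95. This gives 1 − 0.975⁵ = 0.119 and 1 − 0.975²⁰ = 0.397.

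With correlation, simulated z-tests (at least 100,000 draws per setting) give:

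| Correlation between instruments / over time | Any of 20 | Any of 20, favouring programme | Any of 5 at one time |
|---|---|---|---|
| 0 / 0 | 64% | 40% | 23% |
| 0.3 / 0.5 | 54% | 28% | 21% |
| 0.5 / 0.5 | 48% | 25% | 18% |
| 0.5 / 0.7 | 42% | 21% | 18% |
| 0.7 / 0.7 | 35% | 17% | 15% |
| 0.9 / 0.9 | 18% | 9% | 10% |

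For five tests at one time, the favourable-only figure falls from 12% (independent) to about 7% (correlation 0.7).

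**3. Power if five co-equal primaries are kept.**

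- Bonferroni, α = 0.05/5 = 0.01: power for a given instrument at 251 per arm is Φ(2.80 − 2.576) = 0.589 (0.585 with the t distribution). For 80%, n = 2(2.576 + 0.842)²/0.0625 ≈ 374 per arm, and 748/0.75 = 997.3, so 998 in total.
- Holm, if all five instruments share d = 0.25: about 68–70% per instrument, by simulation with correlations of 0 to 0.7.
- All five required at 0.05: 0.80⁵ = 0.33 if independent, and higher with positive correlation.

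**4. Power if self-efficacy is tested first in a fixed sequence.** It is tested at the full 0.05, so step 1 applies unchanged and power stays at 80%.

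**The case against.** The best defence is that the multiplicity method and testing order are commonly left to the analysis plan, which is not shown. An analysis plan could place self-efficacy first and leave the sample size intact. That is correct as far as it goes. But the protocol does more than stay silent: it declares five measures primary and sizes the trial for one. Those two statements need reconciling wherever the detail is finally put.

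Several stronger readings are tempting, and the article does not support them.

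- **A reader might infer that at least 20 tests will be run at 0.05 each.** The article says only that effects are assessed at post-intervention and follow-ups with mixed models. One joint test over time per instrument would leave five. In the other direction, 20 would be too few if the two stress scales or the coping strategies were scored separately.
- **A reader might conclude that a false-positive primary result is likely.** A chance above one half needs about 20 separate tests, low correlation, an any-one-wins rule that is nowhere stated, and no true effect on anything. At moderate correlation the figure is below one half, and some of those results would be against the programme.
- **A reader might say that 80% is not the power of any error-controlled version of this outcome.** Step 4 of the working shows otherwise.
- **A reader might take 59% as the power of Holm's first step.** It is the power for one named instrument at 0.01. The first step asks whether the smallest of five p-values is below 0.01. If all five share d = 0.25 and correlate at 0.3–0.7, that power is about 94% down to 83%.
- **A reader might say that the main result can be picked freely once the data are seen.** The five instruments are prespecified, and researchers are blinded to allocation during the primary analysis. This limits selection by direction, but it does not control the error rate.

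**Conclusion.** The concern holds as a conflict between the definition of the primary outcome and the sample size. Five instruments are co-equal primaries, assessed from T2 to T5 at a general 0.05 with no decision rule. The 80% power belongs to one unadjusted self-efficacy comparison at a time that is not named.

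The inflation figures rest on three assumptions: any one significant result counts as success, there is no true effect, and correlations lie between 0 and 0.7. On that basis the chance of at least one significant primary result is about 15–23% with one test per instrument and about 35–64% with separate tests at four times. Restricted to results favouring the programme, it is about 7–12% and 17–40%. Every setting examined is above 5% for a two-sided claim, and above the one-sided 2.5% for a favourable one. How far above depends on choices that the article does not state.

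**What to change.** Before unblinding, name one primary endpoint at two-sided 0.05. Parental self-efficacy is the natural instrument because it is the only one that the sample size supports. The time point must be declared as well. T2 is reasonable, but the Power calculation does not imply it, so it needs its own justification. With that choice, 251 per arm and 670 in total stand unchanged.

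For the remaining instruments and times, either of these would do:

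- make them secondary, with a stated multiplicity rule that covers both instruments and time points; or
- test the five instruments in a fixed sequence with self-efficacy first, which keeps 80% power for self-efficacy.

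If five co-equal primaries are kept under Bonferroni or Holm, state the success rule and restate the power. It is about 59% for d = 0.25 on a given instrument at 0.01, or about 68–70% per instrument under Holm if all five share that effect.

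The cost is protocol and analysis-plan wording and a registry update, with no new data. The real downside is that the later time points and the other four instruments lose primary status. One of those is emotion regulation, the subject of the first research question in Objectives {7}. If the sponsor regards that question as the main one, it may choose that instrument instead, but it must then give a power basis for it.
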